### Statistical analysis: primary endpoint—impact of male *Wolbachia-Aedes* deployments on dengue incidence, measured by laboratory-confirmed reported dengue case counts normalized by population size in intervention versus non-intervention clusters

We will monitor trends in reported laboratory-confirmed dengue case counts in intervention and non-intervention clusters, before, during, and after male *Wolbachia-Aedes* deployments take place. We aim to use a quasi-experimental approach to examine the impact of male *Wolbachia-Aedes* deployment on routine dengue case notifications normalized by cluster population size. Namely, we will use regression models to model the monthly, normalized dengue case counts across sites; we will control for population size and seasonal variability through weather station observations and autocorrelation between sites by inclusion of lag terms. To estimate the impact of male *Wolbachia-Aedes* deployments on routine dengue case counts, the regression specification will include a binary group variable to denote whether a cluster is an intervention/non-intervention cluster, and a binary treatment variable denoted 1 will be included to indicate when interventions occur within that cluster [55]. Following similar difference-in-difference strategies [56], the interaction term between the group and treatment variables will then yield a coefficient, which provides an estimate of the intervention effect of male *Wolbachia-Aedes* deployments on monthly reported case counts. This approach ensures that extraneous factors and selection bias, such as level changes in dengue case counts in either intervention/non-intervention arms post-intervention are removed [56]. Should pre-trends assumptions in dengue case counts between intervention/non-intervention clusters be violated under this quasi-experimental approach, we will instead use synthetic control methods which can more appropriately identify the impact of male *Wolbachia-Aedes* deployments on routine dengue case notifications.

In both primary endpoints, intention-to-treat analysis will classify all individuals/clusters respectively allocated to the intervention arm in the randomization stage as such, notwithstanding any non-treatment of the intervention clusters. In per-protocol analysis, any dropouts of the intervention clusters will be removed from the analysis, and only intervention clusters receiving intervention treatment as well as the allocated controls will be analyzed.

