### Study design

The study is a parallel, two-arm, non-blinded CR controlled trial conducted in Singapore, an equatorial city-state. Fifteen clusters identified as locations at high-risk of dengue transmission were randomly allocated in an 8:7 ratio to receive the intervention or not. These clusters were residential areas with high-rise public housing apartments, with a high risk of dengue transmission, according to a previous study that mapped the spatial risk of dengue transmission in Singapore [45]. The SPIRIT checklist for the study protocol is provided in Additional file 1.

Under the Infectious Diseases Act [46], all laboratory-confirmed cases of dengue are legally mandated for reporting in the national dengue surveillance system. Approval from the Director of Medical Services has been obtained to collect data of dengue-suspected patients, whose blood samples are sent for dengue tests, through a national network of diagnostic laboratories that support private clinics, public polyclinics, or public/private hospitals. Dengue-suspected patients are identified by clinicians through symptoms such as high fever, body aches, and rashes, coupled with absence of respiratory symptoms. Cases and test-negative controls will be retrospectively classified through laboratory test results. In addition, we will also obtain spatially resolved counts of laboratory-confirmed dengue cases reported to the Ministry of Health.

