Impact on dengue transmission will be assessed in two primary endpoints. In the first primary endpoint, intervention efficacy will be assessed via a test-negative design comparing the *Wolbachia* exposure distribution among dengue cases to the exposure distribution among test-negative controls. We assume that the relative propensity to seek healthcare for undifferentiated febrile illness at any GP clinic, polyclinic, or public/private hospital in the intervention compared to non-intervention clusters is the same for cases and controls; hence, the distribution of male *Wolbachia-Aedes* exposure in the sampled controls will be equal to the distribution of male *Wolbachia-Aedes* exposure in the underlying source population from which cases arose [44, 47]. The odds of male *Wolbachia-Aedes*-exposure among sampled dengue-positive cases relative to concurrently sampled dengue-negative controls is an estimate of the relative incidence of medically attended dengue in intervention versus non-intervention clusters [44, 47]. Should the relative incidence be 1, there could be said to be null treatment effect in intervention clusters. If male *Wolbachia-Aedes* deployments reduce dengue transmission, the relative incidence of laboratory confirmed dengue cases in intervention versus non-intervention clusters is expected to be less than one.

In the second primary endpoint, intervention efficacy will be assessed by comparing laboratory-confirmed dengue case counts normalized by cluster population size (thereafter also referred to as *incidence rate*) between intervention and non-intervention clusters. Here, we assume a quasi-experimental setting, with parallel trends in the dengue incidence rates for both intervention and non-intervention sites in the pre-intervention period. By further specifying the difference (before/after intervention) in differences (intervention vs non-intervention clusters) in a regression setting, we can estimate a level change in dengue incidence rates in both intervention and non-intervention arms in the post-intervention period, thereby removing other secular factors coincident with *Wolbachia-Aedes* deployments which may have influenced dengue incidence rates independently of *Wolbachia-Aedes* deployments. This strategy provides causal identification of the cluster-level intervention efficacy in reducing dengue incidence through the estimate of the level change.

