### Randomized allocation of the intervention

Randomization was conducted in February 2022. Eight out of 15 clusters were randomly selected to receive male *Wolbachia-Aedes* deployments and the rest designated non-intervention clusters. Due to the small number of clusters available for randomization, selection of clusters relied on a constrained randomization strategy to prevent chance imbalances in baseline characteristics between intervention and non-intervention clusters. The proportion of positive to negative dengue samples was used as the constraining variable. A large number of potential random cluster allocations in 8:7 intervention/non-intervention ratio were generated (*n* = 10,000).

For each allocation, the value of the constraining variable was calculated in each study arm using the aggregate arm-level value. Each potential random allocation was evaluated against the pre-defined balancing criteria (i.e., no statistically significant difference in the proportion of positive to negative dengue samples between the two arms) and removed as a potential random allocation if they were not met. All potential allocations that satisfy the balancing criteria were kept (*n* = 3151, exceeding the threshold of 100–150 allocations recommended in the literature), and a single allocation was randomly selected from within the restricted list of balanced allocations. Finally, a single random draw was used to determine which of the two study arms was to receive male *Wolbachia-Aedes* releases. Randomization will be followed by extensive community engagement to seek the support of local politicians and grassroot leaders of each of the eight intervention clusters.

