The CR-TND design is robust to the patients knowing their exposure status to male *Wolbachia-Aedes*-treatment, as long as this knowledge and any attendant modification of health-seeking behavior apply equally to both cases and controls [44]. Even as the study is carried out, other ongoing strategies to reduce mosquito populations in Singapore will continue as usual, such as inspections to detect hotspots of mosquito breeding and community engagement. We will also monitor for potential field establishment of *Wolbachia*, which would hamper the ability of IIT-SIT to suppress mosquito populations. In the event that establishment is observed, male *Wolbachia-Aedes* irradiated for male sterility or male *Aedes aegypti* infected with another incompatible *Wolbachia* strain will be released to mitigate the establishment.

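### The plan says difference-in-differences removes selection bias and level changes in either arm from the case-count endpoint; it removes only fixed differences and shared changes, so an arm-specific change in testing would enter the estimate in full

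*Protocol article*

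**What the plan says.** The Study design section describes a "parallel, two-arm, non-blinded CR controlled trial conducted in Singapore", with fifteen clusters "randomly allocated in an 8:7 ratio to receive the intervention or not". Entry into the data starts with a clinician's suspicion: "Dengue-suspected patients are identified by clinicians through symptoms such as high fever, body aches, and rashes". On notification, the same section says "all laboratory-confirmed cases of dengue are legally mandated for reporting in the national dengue surveillance system". The second primary endpoint therefore counts only people who sought care, were suspected of dengue, were tested and were positive.

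The section on randomized allocation plans "extensive community engagement to seek the support of local politicians and grassroot leaders of each of the eight intervention clusters". The survey section describes its non-intervention arm as having no engagement.

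For the test-negative endpoint, the Discussion calls the design robust to patients knowing their exposure "as long as this knowledge and any attendant modification of health-seeking behavior apply equally to both cases and controls". For the case-count endpoint, the only identifying condition given (Study design, Discussion) is parallel trends before the intervention. The model adjusts for population, weather and lag terms, with synthetic control as the fallback if pre-trends differ. The statistical section for this endpoint then claims: "This approach ensures that extraneous factors and selection bias, such as level changes in dengue case counts in either intervention/non-intervention arms post-intervention are removed". The Study design section, however, says that efficacy is identified through the estimated level change.

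**The concern.** The two statements about the case-count model cannot both stand. If the post-intervention level change identifies efficacy, the method cannot also remove level changes that occur in one arm after the intervention. It has no means of telling a fall in infections from a fall in testing when both begin with the releases and both are confined to the release clusters.

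Testing is the natural candidate for such a change. Residents know whether releases take place where they live, and engagement is directed at the intervention clusters. The test-negative endpoint has a denominator that moves with testing. The case-count endpoint is normalized by resident population, which does not.

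The case-count endpoint is one of two primary endpoints, and the Discussion relies on it to strengthen the causal conclusion given the limits of the test-negative design. Both primary endpoints also enter the interim analyses, where the 50% look can lead to a recommendation to stop or modify the trial. A false statement about what the model removes invites readers to treat agreement between the endpoints as firmer than it is. It also invites them to read disagreement without asking whether testing has shifted.

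**Working it through.** **The plan's own figure.** The section on power for the second endpoint gives at least 31 months post-intervention for 80% power to detect a 50% reduction. It comes from simulations on historical cluster data that are not shown, so it cannot be reproduced here. It is not disputed and is used only to scale the calculation below.

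**Algebra.** Let RR be the true incidence ratio, and r the post-intervention change in testing or care-seeking in intervention clusters relative to non-intervention clusters.

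- Case-count difference-in-differences, ratio scale: any change shared by both arms cancels, leaving observed ratio = RR × r.
- Additive scale: the shift is (r − 1) times the rate the intervention arm would otherwise have had. With an illustrative post-period rate of 150 in both arms and no effect, r = 0.8 gives 150 × (0.8 − 1) = −30.
- Test-negative odds ratio: (RR × r)/r = RR, provided r acts equally on cases and controls.

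**Precision implied by the plan.** Assuming a log scale and a two-sided 0.05 test, 80% power for a 50% reduction implies SE(log RR) = ln 2 / (1.960 + 0.842) = 0.247. For an observed ratio θ, the rejection probability is Φ(−1.960 − ln θ/0.247) + 1 − Φ(1.960 − ln θ/0.247).

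The documents give no value for r; 0.7 to 1.3 is an assumed range.

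| r | Observed ratio, no effect | Rejection, no effect | Observed ratio, true 0.50 | Power | Test-negative OR (no effect / true 0.50) |
|---|---|---|---|---|---|
| 0.7 | 0.70 | 30.2% | 0.35 | 98.9% | 1.00 / 0.50 |
| 0.8 | 0.80 | 14.7% | 0.40 | 95.9% | 1.00 / 0.50 |
| 0.9 | 0.90 | 7.1% | 0.45 | 89.8% | 1.00 / 0.50 |
| 1.0 | 1.00 | 5.0% | 0.50 | 80.0% | 1.00 / 0.50 |
| 1.1 | 1.10 | 6.7% | 0.55 | 67.6% | 1.00 / 0.50 |
| 1.2 | 1.20 | 11.4% | 0.60 | 54.2% | 1.00 / 0.50 |
| 1.3 | 1.30 | 18.5% | 0.65 | 41.4% | 1.00 / 0.50 |

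For r above 1 with no effect, the rejections are mostly in the direction of apparent harm.

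**Do the planned safeguards catch it?** A pre-trend check looks only at the period before releases, when r = 1 by construction. Synthetic control reweights untreated clusters to match the pre-period, so a shift that occurs only in treated clusters after treatment starts remains in the estimate.

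**Could the data show it?** The data collection section says test-negative records with postal codes are obtained, and the power section for the first endpoint refers to historical testing data in the 15 clusters. For a rough volume:

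- 722,204 residents × 51 to 621 per 100,000 gives 368 to 4,485 cases a year.
- At four test-negatives per case, this gives 1,473 to 17,940 a year.
- Over 24 months, split 8:7, the Poisson-only SE of the log arm ratio is 0.037 to 0.011.

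These SEs are too optimistic. They ignore clustering with only 15 clusters, apply national rates to clusters chosen as high-risk, and take a 1600:400 sample requirement as if it were an accrual ratio. They show that counts are unlikely to be the constraint, not what the precision will be.

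**The case against.** The strongest reply is that only one sentence is wrong and that the mechanism is assumed. Much of that stands, and it rules out several stronger readings that a reader might infer.

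- **That testing will shift.** The documents do not show this. The stated purpose of the engagement is local leaders' support, not care-seeking for fever. Routine vector control continues in both arms, tests are done for clinical reasons, and nothing says clinicians use a patient's allocation. Engagement of healthcare institutions for data collection appears in the timeline without reference to arm, and a change common to both arms is what the method does remove.
- **That nothing in the plan could reveal a shift.** Divergence between the two primary endpoints would be a signal, and the secondary cluster-level analysis uses the proportion positive among all tested. But no comparison of the endpoints for this purpose is described, and the data monitoring mentioned concerns response bias and missing data.
- **That the Study design section makes the same error.** Its phrase "thereby removing other secular factors coincident with" deployment is limited, later in the sentence, to factors that act on incidence independently of deployment. A testing change provoked by known releases is not such a factor.
- **That the test-negative endpoint is protected outright.** It is protected only if the change is equal in cases and controls, as the Discussion says.

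It can also be said that an extra sensitivity analysis belongs in an analysis plan not shown here. That is fair for the check taken alone. The finding is the false claim about what the model removes; the check follows from stating the assumption correctly.

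**Conclusion.** The point holds in limited form. The sentence in the case-count analysis section is incorrect and conflicts with the plan's own account of how efficacy is identified. Difference-in-differences removes time-fixed cluster differences and changes shared by both arms, and nothing more. A change in care-seeking or testing that starts with releases in the intervention clusters only would carry through one-for-one, in either direction: less testing inflates apparent efficacy, more testing hides it.

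The sizes rest on assumed values of r, and the rejection and power figures also on a log scale, a two-sided 0.05 test and the stated 80% power being attained. The conclusion is that the estimate is exposed to such a change, not that it will be biased. The correction should be made because it concerns a primary endpoint offered as support for the other.

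**What to change.** 1. Reword the claim so that it covers only time-fixed cluster differences and changes common to both arms.
2. State, as an assumption of the second primary endpoint, that testing and care-seeking do not change differently by arm after releases begin.
3. Check it by fitting the same cluster-month difference-in-differences model to test-negative counts per resident, and to total tests per resident, over the period for which testing data exist and in laboratories that report throughout.
4. Report that estimate with its interval beside the unchanged case-count result, and interpret the latter in its light. Do not let a significance test on it decide which analysis is reported. A version with test-negative counts as offset may be given as a sensitivity analysis only, since it would turn the second endpoint largely into a version of the first.

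The cost is two further runs of a planned model, on records the trial already intends to obtain. The check is limited to network laboratories, which the Discussion says may not be all of them. The pre-period may be shorter than the four years used in the power simulation for case counts. With 15 clusters the precision will be modest, so a null result would not exclude a moderate shift.

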### Power calculations—second primary endpoint

Intervention efficacy in the second primary endpoint from the difference-in-differences strategy as described below, laboratory-confirmed dengue case counts normalized by cluster population size (incidence rate), which is aggregated at the cluster level and measured across months and across clusters. We followed [55] to estimate the required post-intervention duration required to detect a 50% reduction in dengue incidence rates with 80% power.

The power calculation was conducted by performing simulations (*n* = 1000) to estimate the power to detect a 50% intervention effect, assuming eight and seven clusters in the intervention and non-intervention arm respectively, and using historical dengue incidence rate data (2015–2021) in the 15 study clusters. These clusters were constrained randomized to obtain balanced intervention/non-intervention arms as delineated in the preceding section. In each iteration of the simulation, we randomly selected one distinct intervention allocation and 0.5, 1, 1.5, 2, 2.5, and 3 year time frames post-intervention, with pre-intervention period fixed at 4 years and simulated a 50% intervention effect in the intervention arm in the following intervention. The simulated data was analyzed using the difference-in-differences specification (see below) to assess the significance of intervention effect. We then computed the proportion of significant results obtained in each scenario. This provided an estimate for the power of our study and the measurement duration required to obtain the respective power.

We estimate that at least 31 months would be required post-intervention to detect a 50% reduction in dengue incidence rates at 80% power.

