The effectiveness of the trial will also be assessed via a difference-in-differences identification strategy, using laboratory-confirmed dengue cases normalized by cluster population (incidence rates) as the dependent variable. This quasi-experimental analysis complements the randomized trial design by allowing causal inference of the relationship between *Wolbachia-Aedes* deployment and dengue incidence rates, with the proviso that the pre-intervention dengue incidence trends in both intervention and non-intervention clusters are the same [56]. In view of the limitations in our CR-TND design (elaborated in the next paragraph), such as the relatively small total number of clusters and small area of each cluster, including a quasi-experimental analysis would strengthen our conclusions regarding the causal effectiveness of IIT-SIT at reducing dengue incidence in Singapore.

The protocol has several limitations. Firstly, we cannot guarantee that male *Wolbachia*-*Aedes* will not disperse to non-intervention clusters, especially those released near cluster boundaries. This is particularly relevant given the smaller area of each cluster (range 0.53–1.33 km^2^) compared to the Yogyakarta trial. However, our mark-release-recapture studies found that 90% of male *Wolbachia*-*Aedes* were caught within 40 m of release sites [24], suggesting that the mosquitoes would not disperse too far from their release sites. Secondly, we make the simplifying assumption that all dengue infections occur at the residential addresses of test-positive cases. A related point is that we are unable to prevent changes of addresses by residents from intervention to non-intervention clusters and vice versa during the study, which will affect intervention effect estimates by biasing towards the null. Following [44], we address this issue by powering the study to detect a conservative reduction of dengue incidence of 50%, which accounts for any diminishing of effect sizes due to human movements. The total number of clusters in our trial is relatively small, which is why we adopted the constrained randomization strategy similar to that of [44]. Lastly, we might not be able to obtain data from all diagnostic laboratories in Singapore, which introduces the possibility of confounding if blood samples from dengue-infected cases have different likelihoods of being processed in laboratories not within our network.

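### The primary estimator of endpoint 2 (and that of the mosquito endpoints) switches on a pre-trend check that randomisation makes unnecessary

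*Protocol article*

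**What the plan says.** The Study design section introduces endpoint 2 as an assumption: "Here, we assume a quasi-experimental setting, with parallel trends in the dengue incidence rates". The analysis section for that endpoint then specifies a regression of monthly normalised counts, in which the group-by-treatment interaction estimates the effect. It says of this model: "This approach ensures that extraneous factors and selection bias, such as level changes in dengue case counts" are removed. The switch follows: "Should pre-trends assumptions in dengue case counts between intervention/non-intervention clusters be violated under this quasi-experimental approach, we will instead use synthetic control methods". The section on mosquito prevalence repeats it for both species. The Discussion attaches the causal reading to a condition, "with the proviso that the pre-intervention dengue incidence trends in both intervention and non-intervention clusters are the same".

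The section on randomised allocation states: "Eight out of 15 clusters were randomly selected to receive male" deployments. It also says: "The proportion of positive to negative dengue samples was used as the constraining variable". The power section for endpoint 2 simulates the difference-in-differences specification only, "with pre-intervention period fixed at 4 years", and gives at least 31 post-intervention months for 80% power against a 50% reduction.

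**The concern.** The rule replaces the primary analysis. It does not add a second one beside it. In an observational study, parallel pre-trends are the evidence that the two groups are comparable, and failing the check is a reason to change method. Here the comparability of the arms comes from random allocation. A pre-trend difference is what a small randomised trial will sometimes produce, the more so because the constraint was on the test-positivity proportion and not on incidence or its trend.

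Two things are at stake. First, the estimator of one of two primary endpoints is not fixed until someone has judged the pre-period data. Second, if the judgement goes against parallel trends, the trial drops the contrast for which it was powered and uses one with no stated power.

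**Working it through.** **Inputs from the protocol article.** 15 clusters, 8 v 7, randomised; 48 pre-intervention months (4 years); monthly cluster-level rates; 50% reduction, 80% power, at least 31 post-intervention months; 3,151 balanced allocations kept.

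**Assumptions, not in the article.** Two-sided 5% level; log-rate scale; AR(1) monthly errors within cluster, rho 0 to 0.95; a check that is a 5% significance test.

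**Step 1. The plan's own figure.** The 31 months come from simulation on historical cluster data that are not shown, so they cannot be reproduced. They can be used to set precision:

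- Normal formula: SE(log rate ratio) = 0.693 / (1.960 + 0.842) = 0.247.
- Noncentral t, 13 df: 0.229.

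The monthly SD below is chosen at each rho so that the SE equals 0.229.

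**Step 2. How often the check fails when trends truly do not differ.** 4,000 simulated trials per row. The cluster-level check is a t-test of 8 v 7 cluster slopes. The cluster-month check divides the slope difference by sqrt[s²/Σx² × (1/8 + 1/7)], with s² pooled over all cluster-months as if independent.

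| rho | monthly SD | switch, cluster-level check | switch, cluster-month check | DiD type I error, no check | DiD type I error, check passed |
|---|---|---|---|---|---|
| 0 | 1.92 | 5.3% | 5.3% | 5.4% | 5.3% |
| 0.5 | 1.14 | 4.5% | 24.1% | 4.8% | 4.7% |
| 0.8 | 0.71 | 5.3% | 47.8% | 5.0% | 5.1% |
| 0.9 | 0.55 | 5.2% | 60.8% | 4.6% | 4.6% |
| 0.95 | 0.50 | 4.9% | 67.8% | 5.2% | 5.0% |

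A second set of assumed settings (rho 0.7 to 0.85) gave 25 to 42% for the cluster-month check.

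**Step 3. What the check buys.** The last two columns are the same within simulation error. Difference-in-differences tested at cluster level holds about 5% whether or not it is screened, so the check adds no protection.

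**Step 4. What the switch costs.** Simulated with no divergence and seven donors, synthetic control had an SD 8 to 14% larger than difference-in-differences. The mechanism is simple: with equal cluster variances, equal weights on seven controls give the smallest control-arm variance (1/7), and unequal weights give more. Starting from 80% power, and assuming the same form of test:

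- 8% larger: 2.802 / 1.08 = 2.594; 2.594 − 1.960 = 0.634; power about 74%.
- 14% larger: 2.802 / 1.14 = 2.458; 2.458 − 1.960 = 0.498; power about 69%.

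The size depends on the assumed settings and can be smaller. The article does not define the donor pool, so seven donors is also an assumption.

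**The case against.** **The switch is orderly.** One method comes first and one fallback is named. The trigger concerns pre-intervention data, so it need not be influenced by outcomes after release. Intention-to-treat classification covers both primary endpoints, and endpoint 1 has no such switch. All of this stands. It limits the scope of the point, but it does not supply a reason for the switch.

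**Detail left to an analysis plan.** The criterion for a violation and the inference method may well be in a fuller document, and their absence here is not the point. The replacement rule itself is stated in the article.

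**Conditional imbalance.** Randomisation guarantees validity over allocations. Given a visible chance difference, an unadjusted estimate may still be off. That is fair, and it argues for adjusting for pre-period incidence and showing a sensitivity analysis.

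**The cluster-month rates are avoidable.** The planned model has lag terms, and a sensible check would respect clustering. With such a check, chance switching is about 5%.

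Three stronger readings are tempting but not supported:

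- A reader might infer that the plan treats an undetected violation as proof of equal trends. The article speaks of an assumption and a proviso, and describes no such test.
- A reader might infer that, after a switch, p could not fall below 1/8, taking eight treated clusters as one unit against seven single-donor placebos. The article names no such inference. Re-randomising over C(15,8) = 6,435 allocations, or over the 3,151 balanced ones, gives floors of 1/6,435 = 0.0002 or 1/3,151 = 0.0003.
- A reader might count how often a 15-cluster check would miss a drift large enough to mimic an effect. That supposes a real, continuing divergence between arms, whereas under randomisation a difference between arms is chance.

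**Conclusion.** The point holds as a needless, data-dependent replacement of a primary analysis, for endpoint 2 and in the same words for the mosquito endpoints. It does not show that difference-in-differences is invalid; the argument depends on its being valid under randomisation. The chance of an unnecessary switch is about 5% with a cluster-level 5% test. It ranges from 5% to 68% if cluster-months are treated as independent (rho 0 to 0.95). The loss of precision after switching is modest in simulation, and its direction is more secure than its size. All these figures are illustrative: the form of the check, the error structure and the donor pool are assumed. The logical core rests only on the stated 8:7 randomisation and the stated switch. This should be changed, but it does not threaten the trial's validity.

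**What to change.** - In the endpoint 2 analysis section, name difference-in-differences of the randomised arms as the primary analysis without condition. Adjust it for each cluster's pre-period incidence, and test it at cluster level or over the balanced allocations from the randomisation section.
- Show pre-intervention trends by arm descriptively.
- Report synthetic control in every case, as a sensitivity analysis and never as a replacement.
- Delete the replacement sentence there and in the mosquito prevalence section.
- In the Discussion, rest the causal claim on randomisation and not on the pre-intervention trends being equal.

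The cost is wording only, since both analyses use the same incidence series. The downside is that the primary result stands even if a visible chance difference in pre-trends appears. The sensitivity analysis beside it lets readers judge how much that matters.
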